##### Health outcomes (BMI, aerobic fitness, perceived stress)

2.3.2.2

Students’ weight in kilograms to the nearest 0.1 kg (27, 63, 64) and height in centimeters to the nearest 0.1 cm (27, 63, 64) will be recorded using a standard stadiometer and a weighing scale. Body weight in kilograms will be divided by height in meters squared to measure the BMI (27, 63, 64). Students’ age and gender-specified BMI categories will be identified using the calculator introduced by the Ministry of Health in Sri Lanka (65).

The multistage shuttle run/ beep test [66] will be used to measure aerobic fitness, proven highly reliable and valid among school children (32, 66). Results from the test will be used to calculate VO_2_ max using the equation proposed by previous studies (67, 68). Students will be asked to run back and forth on a 20 m course as instructed by a sound signal emitted from a pre-recorded tape, ensuring they touch the 20 m line with their foot (32). The sound signal frequency increases by 0.5 km/h every minute, indicating the next stage (level), starting with a speed of 8.5 km/h. The test ends when participants fail to reach the line before the signal.

Perceived stress will be measured using a translated Sinhala version of the Perceived Stress Questionnaire 8–11 (PSQ8-11 (67)). PSQ8-11 will measure two subscales: perceived psychological stress (nine questions) and physiological stress (10 questions). This 19-item questionnaire requires the students to recall their feelings from the previous week. The students will self-rate their responses on a four-point Likert scale (1 = never, 2 = sometimes, 3 = often, 4 = very often). A higher score on the questionnaire will indicate greater perceived stress (67).

### Fidelity of the intervention

2.4

The primary source for assessing the fidelity will be the logbooks of the teachers. An example of a log sheet can be found in Supplementary material S6. Teachers will indicate how many IcPAB they implemented daily throughout the intervention period. Teachers will be reminded every day via WhatsApp messages to carry out IcPAB, and a research team member will visit the schools once a week to check if the logbooks are duly filled. The personal visits to the intervention schools will also minimize issues with time management and PA breaks implementation from the teachers’ side. In addition, accelerometer data from the post-test will be compared with the responses obtained through teacher and student interviews at the post-test.

### Process evaluation

2.5

During the intervention, the principal investigator will receive teacher feedback and give subjective evaluations on how the teachers implement the IcPAB. At the same time, the research team will obtain verbal feedback once a week from the students on IcPAB’s ability to provide fun and engagement using two close-ended questions: (1) Did you enjoy the activities today? (2) Was it easy for you to follow the instructions and do the activities today? This ongoing feedback-receiving process will be used to overcome any identified or foreseen challenges to implement the IcPAB program (31, 43).

In addition, after the 12-week RCT intervention program, a five-point Likert-scale questionnaire will be distributed among the intervention group’s teachers and students to analyse process evaluation outcomes (Supplementary material S7). The teachers’ questionnaire consists of eight items, while the students’ questionnaire consists of nine items. Both the questionnaires were adopted from previous research work (56, 69).

#### Sustainability evaluation

2.5.1

As a sustainability strategy to track the program for future adoptions all the teacher facilitators and randomly selected student groups will be contacted. The aim is to explore the perceptions of teachers and students in attending and implementing in-classroom PA breaks program through a semi structured interview study based on the capability, opportunity, and motivation behaviors model. The interview guide is available in Supplementary material S8.

### Data analysis

2.6

Data will be statistically analyzed using IBM SPSS software version 28. A randomization check will be performed using independent t-tests (for continuous outcomes) and chi-square (for categorical variables) tests (70). Descriptive statistics such as mean, standard deviation, and percentages will be used to describe the baseline characteristics of the sample and the attrition rates. Primary analysis will be handled with an intention-to-treat modified (m-ITT) approach (71). Missing values analysis will be conducted to observe whether the data are missing completely at random (MCAR). Missing data values will be handled using the multiple imputation method with chained equations.

To test the effectiveness of the IcPAB, generalized linear mixed models (GLMM) will be used by linking to the dependent variables at the individual level (students) and group level (intervention vs. control) with time (pre to post-test) (12, 72, 73). A random intercept will be used to account for the repeated measures of the subjects (35). To test the moderation effects by gender, an interaction test will be conducted via GLMM by setting group-by-time-by-gender as the moderator (35). A 5% level (two-tailed) will be used as the statistical significance cut-off point (74). All the intervention effects will be reported based on the type III tests of fixed effects of GLMM. The estimates of the impact sizes will be written based on the estimated coefficients (*β*) with the 95% confidence intervals/ odds ratio for those estimates based on previous intervention effect report practices for IcPAB (31, 63) in addition to the mean changes in the intervention and control groups. The odds ratio (OR), where OR = 1.68, 3.47, and 6.71 are equivalent to Cohen’s *d* = 0.2 (small), 0.5 (medium), and 0.8 (large), will be used for the interpretations, respectively, (75). Furthermore, a sensitivity analysis to the m-ITT results will be facilitated by considering all the subjects who complete all the baseline and post-test measurements for all the primary and secondary outcomes to ensure the robustness of the primary data assessment and strengthen the conclusions and credibility of the study’s findings.

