### Study design and selection of subjects

2.1

A single-blinded parallel randomized controlled trial (RCT) will evaluate the intervention effects of IcPAB compared to a control group. Target participants will be the fifth graders in government primary schools. Based on the data shared by the Ministry of Health, Sri Lanka, the COVID-19 pandemic severity was slight in the Bandarawela Education Zone (city) in Badulla District. Therefore, the government schools of Bandarawela Education Zone were contacted to initiate the recruitment process in late 2022. The age range of the grade five students is 9 to 10 years old. The targeted population is exposed to 6 hours of regular classroom time (7.30 a.m. to 1.30 p.m.), including a 20-min lunch break according to the government primary school norms in Sri Lanka. Within the government primary school setting, the teacher in charge of a class should teach all subjects in the syllabus for the class, such as mother tongue, mathematics, religion, environment and English. Depending on the interests of the schools, the teachers will conduct additional classes after regular school time to prepare the students for the year-end national scholarship examination. Therefore, the study was designed to be implemented only during the standard classroom time for 12 weeks.

Based on GPower 3.1 software, through *a priori* power analysis, it was estimated to obtain at least 198 participants for both the intervention and control groups to expect an effect size of 0.21 [Cohen’s *f*, converted from *d*, (45, 46)] on academic achievement (mathematics) by providing a power of 0.8 (1-β) with an alpha of 0.05 to test the primary hypotheses of the study with an estimated 10% dropout rate [dropout rates were less than 10% in previous studies (10, 33, 47)] at the post-test/ follow-upstage.

Therefore, it is anticipated to recruit five to six classes (30 to 40 students per class) from two government schools to conduct the study to reach the required minimum sample size. Block randomization technique via MS Excel, will be used to randomize the sample classes by an assessor who is blinded to the intervention content and outcome assessment.

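### The primary outcomes are analysed as group-by-time change rather than as post-test adjusted for baseline, and the stated sample size is not the calculation for that test

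*Protocol article*

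**What the plan says.** The Data analysis section of the protocol article tests effectiveness with a generalised linear mixed model that links the outcome "at the individual level (students) and group level (intervention vs. control) with time (pre to post-test". It adds: "A random intercept will be used to account for the repeated measures of the subjects". Effects come from type III tests of fixed effects and are reported as coefficients with confidence intervals, alongside mean changes per arm. Moderation by gender is a group-by-time-by-gender term. Baseline adjustment is not mentioned. The significance rule is: "A 5% level (two-tailed) will be used as the statistical significance cut-off point".

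The section Study design and selection of subjects sizes the trial on mathematics: "it was estimated to obtain at least 198 participants for both the intervention and control groups". The anticipated effect there is f = 0.21, derived from a d whose value is not shown. The calculation proceeds "by providing a power of 0.8 (1-β) with an alpha of 0.05 to test the primary hypotheses", and 10% dropout is allowed for. It gives no pre-post correlation and does not say which SD the d refers to. The same section randomises classes, five to six of 30 to 40 pupils, from two schools.

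**The concern.** The section does not write out the main treatment term, but group-by-time is the only one that fits. A group main effect would average in the pre-test, when no effect can exist, and moderation is already built on group-by-time. With two waves and a pupil random intercept, that term is the difference between arms in mean change.

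Two things follow. First, the model estimates a separate baseline mean for each arm, although randomisation makes these equal in expectation, and it fixes the weight on baseline at 1 instead of estimating it. That usually costs precision on mathematics and reading. Second, the power of a change contrast depends on the pre-post correlation, which the sample-size statement does not contain. The stated 80% is therefore not a statement about the planned test.

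**Working it through.** **Inputs.** From the protocol: alpha 0.05 two-sided, power 0.80, f = 0.21, total 198, dropout 10%, five to six classes of 30 to 40. Assumed because the protocol does not give them: equal arms, equal pre and post variances, d = 2f = 0.42 on the raw-score SD, pre-post correlation r, intraclass correlation (ICC), and class-level correlation over time.

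**1. Reproducing 198.** Normal approximation: n per arm = 2(1.96 + 0.8416)²/0.42² = 89, so 178 in total, and 178/0.9 = 197.8, or 198. The two-group F test at f = 0.21 has power 0.8002 at 180 completers; 180 × 1.1 = 198 and 180/0.9 = 200. Repeated-measures settings at f = 0.21 do not give 198: the between-arm factor at r = 0.5 needs 136 completers, and the within-between interaction needs 48 at r = 0.5 and 92 at r = 0. The figure is a one-measurement comparison.

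**2. The planned model is a change comparison.** On simulated two-wave data (180 pupils), the random-intercept group-by-time estimate and SE matched the change-score comparison: 0.4377 (SE 0.1576) by both routes at r = 0.3, and 0.3281 (SE 0.1223) by both at r = 0.7. Adjusting for baseline in the same data gave SEs of 0.1395 and 0.1145.

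**3. Independent pupils.** With raw variance 1, the change variance is 2(1 − r) and the baseline-adjusted variance is 1 − r². Their ratio is 2/(1 + r). Power at 180 completers, d = 0.42:

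| r | change | adjusted | variance ratio |
|---|---|---|---|
| 0.3 | 0.658 | 0.836 | 1.54 |
| 0.4 | 0.725 | 0.864 | 1.43 |
| 0.5 | 0.800 | 0.899 | 1.33 |
| 0.7 | 0.951 | 0.975 | 1.18 |
| 0.8 | 0.993 | 0.997 | 1.11 |

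The change contrast reaches 80% at r = 0.50 with 180 completers, and at r = 0.45 if all 198 are analysed.

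**4. Classes randomised.** Write ρc for the correlation of class effects over time, ρw for the within-class pupil correlation, m = 33 pupils per class, and b for the baseline slope (b = ρw approximates a model with a class random effect). Variance of one class mean:

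- change: 2·ICC·(1 − ρc) + 2(1 − ICC)(1 − ρw)/m
- adjusted: ICC·(1 + b² − 2bρc) + (1 − ICC)(1 + b² − 2bρw)/m

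Worked case, ICC 0.10, ρc 0.8, ρw 0.5: change 0.0400 + 0.0273 = 0.0673; adjusted 0.0450 + 0.0205 = 0.0655; ratio 1.03.

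| ICC | ρc | ratio, ρw = 0.5 | ratio, ρw = 0.7 |
|---|---|---|---|
| 0.05 | 0.7 | 1.20 | 1.18 |
| 0.05 | 0.9 | 0.99 | 1.04 |
| 0.10 | 0.5 | 1.33 | 1.25 |
| 0.10 | 0.8 | 1.03 | 1.11 |
| 0.10 | 0.9 | 0.85 | 0.99 |

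Simulation of six classes of 33 agreed: ratios of about 1.02 to 1.30 in most settings, and 0.71 to 1.06 when class means correlated about 0.9.

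**5. Size of the clustering problem itself.** With 36 per class, the design effect 1 + 35·ICC is 1.35 at ICC 0.01 and 4.5 at ICC 0.10. A nominal 80% falls to about 67% and 26%, before any loss of degrees of freedom.

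**The case against.** The strongest reply is that a pre-post mixed model is valid and unbiased under randomisation, so this is a matter of efficiency and not an error. That stands.

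The second reply is that 2/(1+r) belongs to individually randomised pupils, while this trial randomises intact classes. Change removes stable class differences in full; a pupil-level slope below 1 removes only part of them. This stands too. A reader might infer from step 3 that adjusted intervals would be 5% to 19% narrower (r from 0.8 to 0.3). The documents do not support that for this trial, since step 4 shows the gain shrinking to a few percent or reversing. Nor can one say in general that adjustment protects better against chance imbalance between five or six classes: the change contrast already subtracts the baseline difference, and which method does better depends on ρc.

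The third reply is that the r = 0.5 threshold needs d on the raw-score SD. If d were scaled to the SD of change, power would not depend on r. The protocol does not say which. This stands as a limit on the power figures, but it does not explain the sample size: the calculation that reproduces 198 has no repeated measure in it.

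**Conclusion.** The point holds in a limited form. The planned effect is a change contrast, baseline is not used as a covariate, and the stated N does not belong to the planned test. Baseline adjustment would usually be as precise or more so: 0 to 30% in variance under the assumed ICC and correlations, with a possible loss if class-level correlation is about 0.9.

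A reader might conclude that the trial misses its 80% power because of this choice. The documents do not support that. A shortfall from this source requires r below about 0.5, d on the raw-score SD and independent pupils. The first two are not stated and the third is contradicted by class randomisation. At r = 0.7 the pupil-level difference is only 0.951 against 0.975. The power loss from randomising classes is a separate and larger problem, which baseline adjustment alone does not solve.

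**What to change.** For each continuous primary outcome, define the primary contrast as the difference between arms at post-test adjusted for the pupil's baseline score on the same measure, with a class random effect and small-sample degrees of freedom. The corresponding common-baseline mixed model, with class and class-by-time random effects, would also serve. Report the adjusted mean difference with its 95% confidence interval, and keep group-by-time change as a supportive analysis. In the sample-size paragraph, state the assumed pre-post correlation and the SD to which d refers, so that the 80% can be tied to the test that will be run.

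No new data are needed: baseline scores are already collected, and the planned multiple imputation covers pupils without one. The cost is more than wording, however. With five to six classes in two arms, a class-level comparison has about 5 − 2 = 3 to 6 − 2 = 4 degrees of freedom, and intervals will show that. Class randomisation imposes this under either analysis. There may also be a loss of precision if class differences prove highly stable over the 12 weeks.

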### Limitations

3.1

Despite the strengths mentioned above, it is possible to indirectly affect the fidelity of the intervention due to the ongoing economic crisis and post-COVID-19 pandemic in Sri Lanka (83, 84). For example, the sudden closure of schools for a few days will reduce the number of days the IcPAB can be implemented weekly (83–85). Furthermore, participants were limited to the Uva Province in Sri Lanka. This will cause a representation bias in the data (86). The classes are randomized into intervention and control groups. This may cause potential contamination effects. Therefore, use of a cluster-RCT design is recommended to in the future studies similar to a previous study (31). There may be a potential for bias as the same teacher who is delivering the IcPAB records the fidelity of the intervention (12) even though the research team plans to conduct weekly observations of the frequency of conducting IcPAB. Also, the results may be limited by poor protocol compliance if few classes are included in the study as “one teacher could skew the results” (31).

Even though, this study was designed based on COM-B model to address the hindrances to implement classroom-based PA, effect of the factors such as participants’ dietary habits (87), challenges with school initiatives (88), children’s preferences for outdoor activities (89) will not be measured throughout the proposed RCT.

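### Whole classes are randomised but the planned mixed model names only a student random intercept, so any class-by-time variation makes the 5% group-by-time test anti-conservative

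*Protocol article*

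**What the plan says.** **Unit of randomisation.** Section 2.1 (Study design and selection of subjects) says "Block randomization technique via MS Excel, will be used to randomize the sample classes by an assessor". The Limitations section repeats it: "The classes are randomized into intervention and control groups".

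**Number of units.** Section 2.1 also says "it is anticipated to recruit five to six classes (30 to 40 students per class) from two government schools".

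**Why a class shares its progress.** In these schools "the teacher in charge of a class should teach all subjects in the syllabus for the class". The same teacher delivers the breaks to every student in an intervention class. The Limitations section accepts that with few classes "one teacher could skew the results".

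**Model.** Section 2.6 (Data analysis) links the outcomes "at the individual level (students) and group level (intervention vs. control) with time (pre to post-test"). It names one random effect: "A random intercept will be used to account for the repeated measures of the subjects (35"). Intervention effects are to be reported from type III tests of fixed effects at a two-sided 5% level. The article mentions no class or school effect, cluster-robust variance, ICC or small-sample correction.

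**The concern.** The model treats about 180 students as if each had been randomised separately, when the independent units are five or six classes. A student random intercept absorbs the correlation between one child's two measurements. It does nothing about classmates who share a teacher and therefore tend to gain, or fail to gain, together over the 12 weeks.

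With two or three classes per arm, one effective teacher in the intervention arm can produce a group-by-time difference that the model takes for a programme effect. Mathematics and reading, the two primary outcomes, are the measures on which a teacher's influence over a term is most plausible. The confidence intervals would be too narrow in the same way.

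**Working it through.** **1. The plan's own sample size.** Inputs from section 2.1: Cohen's f = 0.21, power 0.80, alpha 0.05, dropout 10%. For two equal groups d = 2f = 0.42 (1:1 allocation is my assumption).

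n per arm = 2 × (1.960 + 0.842)² / 0.42² = 88.99, so 89 per arm and 178 in total. 178 / 0.9 = 197.8, so 198.

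This matches the stated 198. It is reached with students treated as independent (design effect 1), so the sample size makes no allowance for classes either.

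**2. Which class variation matters.** The effect is tested as group-by-time. With two waves and complete data, that test under a student random intercept is equivalent to comparing change scores between arms. A class effect that is the same at both waves drops out of the change. In simulation with a stable class ICC of 0.10 and no class-by-time variance, the test rejected in 5.2% (six classes of 33) and 5.3% (five of 40) of null trials. Only class-by-time variation inflates the error, so the ICC that counts is that of the pre-post change.

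**3. Type I error, full-sample outcomes.** The ICC values are assumed. With m students per class, the design effect is DE = 1 + (m − 1) × ICC, the model's standard error is 1/√DE of its true value, and the true alpha is 2 × [1 − Φ(1.96/√DE)].

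| ICC of change | m = 30: DE | SE ratio | true alpha | m = 36: DE | SE ratio | true alpha |
|---|---|---|---|---|---|---|
| 0.01 | 1.29 | 0.88 | 0.084 | 1.35 | 0.86 | 0.092 |
| 0.02 | 1.58 | 0.80 | 0.119 | 1.70 | 0.77 | 0.133 |
| 0.05 | 2.45 | 0.64 | 0.211 | 2.75 | 0.60 | 0.237 |
| 0.10 | 3.90 | 0.51 | 0.321 | 4.50 | 0.47 | 0.356 |

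Simulation of six classes of 30 and five of 36 agrees to within about a percentage point or so. A t-test on class mean changes with k − 2 df (k = number of classes) stayed at about 5% throughout. As a check on the equivalence in step 2, fitted mixed models with a student intercept only (six classes of 33, 200 runs each) rejected in 6%, 24% and 40% of null trials at ICC 0, 0.04 and 0.10.

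**4. Accelerometer outcomes.** Section 2.3.2.1 limits these to a subsample of 47, which is 47/6 = 7.8 or 47/5 = 9.4 per class if spread evenly. The same formula gives true alpha of 0.066–0.070 at ICC 0.02, 0.091–0.100 at 0.05 and 0.131–0.149 at 0.10.

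**5. Power of a valid test.** This is a t-test on class means with k − 2 df and 178 evaluable students, taking d = 0.42 in units of the SD of the analysed contrast. The variance of a class mean is ICC + (1 − ICC)/m, with m = 178/k.

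Six classes, ICC 0: m = 29.67; SE = √[(1/29.67) × (1/3 + 1/3)] = 0.150; noncentrality 0.42/0.150 = 2.80; critical t (4 df) = 2.78; power 0.56.

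Five classes, ICC 0: m = 35.6; SE = √[(1/35.6) × (1/2 + 1/3)] = 0.153; noncentrality 2.75; critical t (3 df) = 3.18; power 0.47.

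| ICC | six classes | five classes |
|---|---|---|
| 0 | 0.56 | 0.47 |
| 0.01 | 0.47 | 0.38 |
| 0.02 | 0.40 | 0.31 |
| 0.05 | 0.28 | 0.22 |
| 0.10 | 0.20 | 0.15 |

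**The case against.** **The article may simply be condensed.** It states one purpose for one random intercept and does not exclude further terms, and a fuller analysis plan may exist. This carries some weight but does not remove the point. The article goes beyond silence: it defines the group level as arm and says what the random intercept is for. It also recommends a cluster-randomised design for future studies, so it does not treat this class-randomised trial as clustered. The sample size is consistent with that.

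**The inflation is conditional.** This stands in full. A reader might infer that any resemblance among classmates invalidates the test, or that every p-value in the trial is wrong. The documents do not support that. Stable class differences cancel, and nothing in the article shows that every secondary outcome, BMI for example, varies by class over time.

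**The size is assumed.** This also stands. No ICC is given, so the figures are a range. Much larger inflation follows from an ICC of change of 0.20, but nothing in the documents points to that value. The full-sample figures must not be carried over to the accelerometer outcomes, where classes contribute eight or nine children each.

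**The obvious repair fails.** A reader might conclude that adding a class random intercept to the pre/post model is enough. It is not, because that term cancels from the tested contrast just as a stable class effect does.

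**Conclusion.** The stated model does not match the stated randomisation, and this needs correcting before analysis. With any class-by-time variance, the group-by-time test is anti-conservative and its confidence interval too narrow. Even an ICC of change of 0.01 takes the 5% test to about 8–9% for full-sample outcomes. At 0.10, about one null trial in three would be declared positive (32–37% across the calculations). The accelerometer outcomes are affected less, at about 7%, 9% and 14% for ICC 0.02, 0.05 and 0.10.

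These sizes rest on assumed ICCs, equal class sizes, complete data and near-equal allocation of classes. The direction rests only on classes progressing differently, which is likely for taught subjects with one teacher per class. The sample size has the same gap, so correcting the model also exposes a power shortfall.

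**What to change.** Analyse by the randomised unit and describe the trial as cluster (class) randomised. Any one of these would serve as the primary model:

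- post-test score on arm and baseline score, with a random class intercept;
- the planned pre/post model, with class and class-by-time random effects added to the student intercept;
- a class-level test on mean change.

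Use small-sample degrees of freedom (Kenward-Roger or Satterthwaite for the mixed models). The between-class df are k − 2, that is 3 to 4, without a school term and k − 3, that is 2 to 3, with one. The two-sided critical t is then 2.78 at 4 df, 3.18 at 3 df and 4.30 at 2 df.

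Include school as a fixed effect only if each school has classes in both arms. The article does not say that randomisation is within school, and sections 2.2.3 and 2.4 refer to control and intervention schools. If arm and school coincide, the two effects cannot be separated. Carry class into the imputation model as well.

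**Cost.** No new data are needed beyond class identifiers, but confidence intervals widen and the 80% power statement must be restated. At d = 0.42 a valid class-level test has about 0.56 (six classes) or 0.47 (five) power at ICC 0 and 0.28 or 0.22 at ICC 0.05, and less with a school term. The number of classes should be reconsidered if recruitment still allows; otherwise the article should say that the trial is underpowered for its target effect.

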**Methods:**

The study will adopt a randomized controlled trial (RCT), comprising an in-classroom physical activity breaks program group and a control group to evaluate the effects of IcPAB on academic achievement, movement behaviors and health outcomes. The intervention design is based on the capability (C), opportunity (O) and motivation (M) behavior (B) (COM-B) model. A least 198 fifth graders will be recruited from two schools in Uva province, Sri Lanka. The recruitment process will start in late 2022. Class teachers of the intervention group will implement 5-min activity breaks at least three times a day after completing a training session. The primary variables include mathematics and reading achievement. The secondary variables include physical activity levels, steps count, sedentary behavior, body mass index, aerobic fitness, and perceived stress. Data collection will be implemented at pre-test and post-test, respectively. Intervention fidelity and the process will also be evaluated.

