Therefore, there is a need for more IcPAB initiatives integrated into the curriculum across different geographic locations/ cultures (37) that require shorter bouts of time [i.e., around 5 minutes (12, 43)] with strong methodological quality (39, 44), outcome and process evaluation procedures and theoretical underpinnings (37, 39, 44). Also, the moderating effects of gender on the intervention should be further examined. Thus, by addressing the research limitations, this study aims to develop, implement, and evaluate a 12-week IcPAB program among grade five primary school children in Sri Lanka.

Depending on the aforementioned rationale, the specific research questions of this study include: (1) What is the impact of the IcPAB intervention on the primary outcome, academic achievement (mathematics and reading achievement) during the school day? (2) What is the impact of the IcPAB intervention on the secondary outcomes, movement behaviors (PA levels, steps count and sedentary behavior) and health outcomes (BMI, aerobic fitness, and perceived stress) during the school day? It is hypothesized that the IcPAB group will show improvement in all measures compared to the control group.

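### Mathematics and reading are both primary and tested at a flat two-sided 5%, with no either-or-both success rule; if either suffices, family-wise error is above 5% and at most 9.75%

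*Protocol article*

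**What the plan says.** The abstract (Methods) states: "The primary variables include mathematics and reading achievement". The Introduction puts the primary research question in the singular but with two components: "What is the impact of the IcPAB intervention on the primary outcome, academic achievement (mathematics and reading achievement) during the school day". Sections 2.3.1.1 and 2.3.1.2 describe two separate tests, and no combined score is defined. The hypothesis in the Introduction is general: "It is hypothesized that the IcPAB group will show improvement in all measures compared to the control group".

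Section 2.6 fixes the threshold once, for every outcome: "A 5% level (two-tailed) will be used as the statistical significance cut-off point".

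The sample size paragraph in section 2.1 takes a Cohen's f of 0.21 "on academic achievement (mathematics) by providing a power of 0.8" and applies the whole alpha: "by providing a power of 0.8 (1-β) with an alpha of 0.05 to test the primary hypotheses of the study". It refers to hypotheses in the plural, but gives an effect size for mathematics only.

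The article states no testing order, adjustment, composite or either/both rule for the two primary outcomes.

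**The concern.** With two primary outcomes, a 5% cut-off for each test and no rule linking them, the text permits a positive conclusion on academic achievement from whichever outcome reaches significance. The error rate of that conclusion is then not the 5% that the plan states and that the sample size assumes.

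The opposite reading has its own cost. If both outcomes must be significant, the error is controlled, but the 80% power was derived for mathematics alone and does not describe the chance of winning on both. Until the success rule is written down, either the stated alpha or the stated power does not belong to the primary conclusion. A rule chosen after the results are known would not repair this.

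**Working it through.** **Inputs from the article:** two primary outcomes (abstract; section 2.3.1); two-sided alpha 0.05 (section 2.6); alpha 0.05, power 0.80, f = 0.21 for mathematics, 10% dropout and a total of 198 (section 2.1).

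**Assumptions:** 1:1 allocation; test statistics jointly normal under the null; each test holds its own 5% level; correlation between the two test statistics unknown, so a range is shown.

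**1. Reproducing the 198.** For two equal groups d = 2f = 0.42.
- Normal approximation: n per arm = 2 × (1.960 + 0.842)² / 0.42² ≈ 89, or 178 in total; 178 / 0.9 = 197.8, rounded up to 198.
- Exact F test: 180 in total; 180 × 1.1 = 198, or 180 / 0.9 = 200.

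The stated figure is reproduced with alpha undivided, so it contains no allowance for a second primary outcome.

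**2. Error if either outcome suffices and neither is affected.** Independent tests: 1 − (1 − 0.05)² = 0.0975. Correlated tests: 1 − P(|Z₁| < 1.96 and |Z₂| < 1.96), with correlation r. For benefit only, the upper 2.5% tail of each test is counted: 1 − P(Z₁ < 1.96 and Z₂ < 1.96).

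| Assumed r | At least one false positive, either direction | False claim of benefit only |
|---|---|---|
| 0 | 9.75% | 4.94% |
| 0.3 | 9.5% | 4.8% |
| 0.5 | 9.1% | 4.5% |
| 0.7 | 8.4% | 4.2% |
| 0.8 | 7.8% | 3.9% |
| 0.9 | 7.0% | 3.5% |

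The reference values are 5% for the middle column and 2.5% for the right-hand one. Both sets of scores come from the same children, so a positive correlation is likely, but the article gives none.

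**3. Fixed sequence, mathematics then reading.** Reading is tested only after mathematics is significant.
- If neither outcome is affected, any false claim requires a false rejection for mathematics first: at most 5%.
- If mathematics is truly affected and reading is not, the only possible false claim is on reading: at most 5%.

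The test of mathematics still uses alpha 0.05, so the 198 and its power stand as planned.

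**4. Cost of splitting alpha.** Power for mathematics at two-sided 0.025, with d = 0.42:
- 90 evaluable per arm: Φ(0.42 × √45 − 2.241) = Φ(0.576) = 0.718
- 89 evaluable per arm: Φ(0.42 × √44.5 − 2.241) = Φ(0.560) = 0.712

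Restoring 80% at 0.025 needs 108 per arm, or 216 in total; 216 / 0.9 = 240 recruited (exact F test: 220 and 245). Under Holm the smaller p-value faces 0.025. So 71-72% is the power for mathematics when reading does not pass first; if reading does, mathematics is tested at 0.05.

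**5. If both must be significant.** The error is at most 5% without adjustment. With 90 per arm, power for mathematics is about 0.804. If reading had the same effect and the tests were independent, joint power would be 0.804² ≈ 0.65. The article gives no effect size for reading, so this is illustrative only.

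**The case against.** The strongest reply is that nobody has said either outcome will do. The article's wording is joint: the Introduction hypothesizes improvement in all measures, and the Discussion states the aim as effects on mathematics and reading together. If both are required, there is no inflation. If each is reported strictly as its own claim, each keeps its own 5%. The either-suffices rule is indeed permitted by the text, not stated in it. But the hypothesis cannot serve as a both-required rule, because it covers every secondary outcome as well, and section 2.6 applies its cut-off without any joint condition.

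A reader might infer that this trial's chance of a false claim on academic achievement is nearly 10%. The documents do not support that. The value needs independent tests as well as the either-suffices rule, and it counts false findings of harm along with false findings of benefit. It also takes for granted that each test holds 5%. Classes are randomized, while section 2.6 names a random intercept only for repeated measures of subjects. That is a separate issue, and the figures here neither include it nor correct for it.

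A third reply is that an analysis plan, not shown, may order or adjust the tests. It may, and that would settle the matter. The point rests on what the article itself fixes: two primary outcomes, a flat 5% and a sample size built on undivided alpha. A later plan that split alpha would no longer match the 198.

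Finally, sizing on mathematics does not rank it above reading; section 2.3.1 presents the two as equally important. That is fair. Putting mathematics first is a choice that suits the existing sample size, not something the article already decides.

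**Conclusion.** The point stands in conditional form. The success rule for two primary outcomes is undefined, and the flat 5% threshold, followed as written, allows either one to be declared significant. If either can support a claim on academic achievement and each test holds its level, family-wise error is above 5% and at most 9.75%, or about 9.5% to 7.8% for assumed correlations of 0.3 to 0.8. For false claims of benefit it is up to about 4.9% against 2.5%. The upper end is a ceiling for independent tests, not an estimate for this trial. If both outcomes are required, the error is controlled, but the 80% power does not apply to the joint claim. The change is worth making before outcome data are seen and costs little.

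**What to change.** Add a rule to section 2.6: mathematics is tested first at two-sided 5%; reading is tested at 5% as confirmatory only if mathematics is significant, and is otherwise reported descriptively with its estimate and confidence interval. This takes one sentence, keeps the total of 198 and leaves alpha for mathematics unchanged. The small downside is that reading cannot be claimed on its own if mathematics fails.

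Two alternatives are acceptable if the investigators prefer them, provided their cost is stated:
- **Holm across the two outcomes.** Either can then be claimed alone, but power for mathematics can fall to about 71-72%. Guaranteeing 80% at the 2.5% level would need about 240 participants.
- **Both required.** No alpha adjustment is needed. Section 2.1 should then give an effect size for reading and an assumed correlation, and restate power for the joint claim.
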